## Abstract

**Highlights:**

**Public health relevance—How does this work relate to a public health issue?**
Insomnia is highly prevalent in mild cognitive impairment and dementia and is associated with accelerated cognitive decline, increased morbidity, and healthcare utilisation.This study addresses sleep disturbance as a potentially modifiable behavioural risk factor for dementia, a public health priority, using a scalable digital intervention.

**Public health significance—Why is this work of significance to public health?**
By evaluating the feasibility of a digital cognitive behavioural therapy for insomnia (dCBT-I) in cognitively impaired adults, this trial explores a low-cost, non-pharmacological strategy to improve sleep, while potentially slowing functional and cognitive deterioration.The intervention may reduce the reliance on sedative–hypnotic medications, thereby supporting deprescribing initiatives and reducing the fall risk, polypharmacy, and medication-related harm in older adults.

**Public health implications—What are the key implications or messages for practitioners, policy makers, and/or researchers in public health?**
If feasible, digitally delivered dCBT-I could be integrated into routine memory clinic pathways as a scalable and accessible adjunct to standard dementia care.Findings will inform the design of a definitive trial and contribute to emerging dementia prevention and brain health strategies that incorporate sleep as a core intervention target.

**Abstract:**

Dementia is a leading and growing cause of disability worldwide. Insomnia is highly prevalent in mild cognitive impairment (MCI) and dementia and is associated with impaired cognition, functional decline, and reduced quality of life (QoL). Although sleep disturbance represents a potentially modifiable risk factor within the trajectory of cognitive impairment, there have not been many studies conducted to examine the feasibility or preliminary efficacy of digital cognitive behavioural therapy for insomnia (dCBT-I) in this population. The aim of this pilot randomised controlled feasibility study is to evaluate the acceptability, adherence, and potential clinical effects of a multi-component dCBT-I programme (Sleepio) in adults with MCI or mild dementia and comorbid insomnia. Thirty community-dwelling adults aged ≥50 years with established MCI or mild dementia (Mini-Mental State Examination ≥18; Clinical Dementia Rating 0.5–1.0) and insomnia (Sleep Condition Indicator ≤16) will be randomised (1:1) to Sleepio or a wait-list control. Feasibility outcomes include recruitment and retention rates, intervention adherence (completion of ≥4/6 sessions), and acceptability measured using validated usability scales. Secondary outcomes include changes in sleep, mood, QoL, cognition, and function over 10 weeks. Adverse events will be monitored to assess safety. Findings will inform the design of a future definitive trial evaluating digital sleep interventions in cognitively impaired populations. Ethical approval has been granted. The trial is registered at ClinicalTrials.gov (NCT07363928).

## 1. Introduction

Sleep, and receiving the recommended amount (an average of 7 to 9 h) of it, is important for overall physical and mental health for persons at all ages of life but particularly as we age [1,2]. From middle age onwards, a typically U-shaped pattern is seen, with a shorter and longer sleep duration associated with greater cognitive impairment [1]. The prevalence of sleep disturbances including insomnia increases in older age, with increased frailty and greater multi-morbidity [2,3,4]. Insomnia impacts negatively on physical and mental health [5] and is associated with a decline in cognitive performance [6]. Two recent meta-analyses suggest that insomnia increases the risk of developing dementia [7,8]. In addition to epidemiological associations, emerging mechanistic evidence further supports a bidirectional relationship between sleep disturbance and neurodegeneration [9]. Experimental models suggest that sleep plays a critical role in the clearance of neurotoxic metabolites, including β-amyloid and tau proteins, via the glymphatic system [10]. The disruption of slow-wave sleep in particular has been associated with increased amyloid deposition, impaired synaptic plasticity, and neuroinflammation [11]. Human neuroimaging studies similarly demonstrate associations between reduced sleep efficiency, increased sleep fragmentation, and greater amyloid burden [12]. These findings raise the possibility that chronic insomnia may not only be a consequence of neurodegenerative processes but may also contribute to their progression. Further, sleep disturbance is also associated with impaired attention, executive function, and memory consolidation [13], domains commonly affected in mild cognitive impairment (MCI), a prodromal state before dementia, and mild dementia. Therefore, insomnia may exacerbate the existing cognitive vulnerability in this population, compounding functional decline and caregiver burden. Targeting insomnia may thus represent a modifiable risk factor within the trajectory of cognitive impairment.

Medications used to manage insomnia are commonly used but associated with multiple different adverse outcomes including a heightened likelihood of delirium, depression, falls, and even higher mortality [14]. In addition, some research suggests that sleep medications including benzodiazepines and so-called “z drugs” may have detrimental effects on cognitive functioning in this population [15]. Further, a recent meta-analysis suggests that these medications are associated with incident dementia including Alzheimer’s disease [16]. Accordingly, there has been a growing emphasis on avoiding hypnotics among older patients and those with cognitive impairment by identifying and evaluating alternative non-pharmacological interventions for insomnia at all ages but especially in older individuals with cognitive decline including dementia [17]. The role of new pharmacological therapies, including orexin receptor antagonists with potentially improved safety profiles compared to traditional hypnotics, have the potential for use in this population but are yet to be studied in detail [18].

Cognitive behavioural therapy for insomnia (CBT-I) is widely endorsed as a first-line therapy for insomnia for which there is a robust and growing evidence base for an effect on sleep. Despite this, we have not found any studies that have shown an effect on cognition and the majority have been conducted in persons with normal cognition [19,20,21,22]. A large systematic review and meta-analysis of sleep interventions in individuals with cognitive impairment incorporated just two small studies of CBT-I, both of which reported significant improvements in sleep-related outcomes [23]. One study, involving 28 individuals with MCI and comorbid insomnia living in independent accommodation, demonstrated significant benefits across objective as well as subjective sleep measures, as assessed using wrist actigraphy and a screening tool called the Insomnia Severity Index (ISI), respectively [24]. By contrast, the results of the second study, which included 35 participants with MCI recruited from outpatient services, did not reveal improvements in objective sleep parameters, although subjective sleep quality showed significant gains [25]. Importantly, participants in this latter study did not exhibit marked baseline sleep disturbances that could account for the absence of an overall effect in the meta-analysis. In light of the positive findings from the study involving participants with baseline insomnia, further investigation into the use of CBT-I for those experiencing cognitive decline is warranted.

Despite its established efficacy, access to CBT-I remains constrained, due to the costs, limited access, time restraints, and insufficient availability of trained clinicians [26]. Digital delivery formats may help address these limitations by offering advantages such as scalability, lower costs, consistent implementation, and remote accessibility. For older adults who experience mobility difficulties or reside in geographically remote areas, these approaches may reduce barriers to treatment access. Digital CBT-I (dCBT-I) therefore represents a potential alternative to conventional therapist-led CBT-I. Evidence from meta-analyses supports the effectiveness of dCBT-I among adults (without cognitive impairment) [27,28], and more recent studies indicate that it is both feasible and beneficial for older adults [29]. A small mixed-methods investigation involving 12 participants provided the initial evidence for the acceptability of dCBT-I, using the Sleep Healthy Using the Internet for Older Adults Suffering with Insomnia and Sleeplessness (SHUTi OASIS) measure (see NCT03213132), with older individuals diagnosed with MCI [30]. The trial using SHUTi OASIS had several limitations; no patients with dementia were included and it was a single-arm design with a highly selected sample of motivated individuals, with an increased risk of bias [30]. In addition, a non-blinded open-label randomised controlled trail (RCT) assessing feasibility reported that a dCBT-I (Sleepio^TM^ version 2.0) reduced ISI scores among individuals with MCI [31]. Sleepio is a dCBT-I programme that has demonstrated effectiveness in treating insomnia [32,33], leading to improvements in self-reported cognition [34], and has demonstrated efficacy at improving sleep specifically among older patients [35]. Based on its evidence, Sleepio is endorsed by the United Kingdom’s National Institute for Health and Care Excellence or NICE as a first-line intervention for the treatment of insomnia [36]. However, again, none of the patients included had dementia and, as the study was performed entirely remotely, it is likely that participants had more mild deficits and were sufficiently familiar with digital technologies to engage with the intervention in a meaningful way, raising the risk of selection bias.

In addition, although these two studies showed feasibility, questions about digital exclusion, usability challenges, selection bias favouring more motivated patients, and uncertainty over sustained engagement among individuals with cognitive impairment, remain unanswered. Further, caregiver involvement may be necessary for some participants, raising important considerations regarding co-design, accessibility, and support structures. The rigorous evaluation of feasibility parameters, including adherence, usability metrics, and qualitative acceptability, will therefore be critical in determining whether dCBT-I can be successfully implemented in routine clinical practice for this population.

### Aim and Objectives

As previous studies were limited exclusively to individuals with MCI, there is a need to include and study feasibility with patients with mild dementia. While, at these stages, individuals typically retain sufficient insight, learning capacity, and functional independence to engage meaningfully with structured behavioural programmes, it is also important to understand the role of and need for caregivers or supporters in engaging with dCBT-I using a hybrid support model. It is similarly necessary to examine whether such an intervention is acceptable and safe in this population, and to estimate the preliminary effect sizes to inform the design and power calculation of a future definitive (Phase III) trial. Thus, the overall aim of this project is to conduct a pilot randomised controlled feasibility study of a dCBT-I intervention (i.e., Sleepio), in patients attending a university hospital memory clinic with MCI or mild dementia, with the following objectives: (1) to determine participant (patient and study partner if deemed suitable) recruitment, retention, and adherence rates; (2) to assess the usability and acceptability of the intervention by analysing overall participant satisfaction and the frequency of adverse events; (3) to examine pre/post-intervention changes in sleep; (4) to examine the effects on psychosocial health including mood; and (5) to examine pre- and post-intervention changes in cognition and function.

## 2. Materials and Methods

### 2.1. Design

REST is an investigator-blinded, randomised, controlled, two-arm, parallel feasibility study. Participants will be allocated in a 1:1 ratio to either the intervention group or a true wait-list control group through a centrally managed, computer-generated randomisation process. An asymptotic maximal randomisation strategy, with a maximum tolerated imbalance of three, will be employed. The study coordinator will not be blinded to group allocation, as this is necessary to deliver training on the intervention to participants in the intervention arm. In contrast, data collectors and controllers, statisticians, and site investigators will remain blinded to treatment assignment. Participants will be randomised in a 1:1 ratio using a computer-generated sequence. Allocation concealment will be ensured using sequentially numbered, opaque, sealed envelopes.

Baseline variables recorded will include demographic information (such as age, sex, ethnicity, employment status, and education status), lifestyle factors (such as smoking history, level of physical exercise, caffeine, and alcohol consumption), medical co-morbidities, and regular medications. The principal investigator, an attending/consultant physician, will adjudicate on medical inclusion and exclusion criteria. Assessment of outcome measures will take place at baseline and post-intervention, which will be set at 10 weeks post randomisation. Participants assigned and randomised to the intervention group will continue to receive treatment as usual in addition to the intervention described in the next section. Those assigned to the wait-list control group will be told that they will receive the intervention at the end of the 10-week study period. They will receive ‘treatment-as-usual’ during the study period.

### 2.2. Intervention and Comparator

Sleepio is a personalised and fully automated dCBT-I intervention programme designed specifically to manage and treat insomnia based on established evidenced cognitive behavioural techniques. It incorporates cognitive and behavioural interventions in conjunction with sleep hygiene education and relaxation techniques. The intervention is delivered via an automated digital platform that uses underlying algorithms to personalise the content, guidance, and support provided to each participant. This tailoring is informed by individual responses to a baseline sleep assessment questionnaire, as well as ongoing data captured through daily sleep diary entries completed throughout the programme. In this way, the intervention dynamically adapts to the user’s sleep patterns and reported difficulties, allowing for a more individualised and responsive therapeutic experience.

The programme comprises six structured sessions, each typically lasting between five and twenty minutes. Following completion of the initial session, subsequent sessions are released sequentially at weekly intervals, thereby encouraging gradual engagement with the intervention over time. While the programme is designed to be completed over a minimum period of six weeks, user engagement patterns suggest that most participants take approximately 9–10 weeks to complete all sessions. Importantly, there is no strict time limit imposed on completion, and, once sessions are unlocked, they remain accessible for repeated viewing, enabling participants to revisit content as needed to reinforce learning and support behavioural change. Participants and/or their study partners will be offered daily SMS messages/emails to support compliance and adherence.

Because the intervention is delivered digitally, participants’ level of digital literacy will be evaluated prior to randomisation using the Mobile Device Proficiency Questionnaire [37]. All individuals assigned to the intervention group will then receive a training/orientation session to support their use of the Sleepio programme. They will also be provided with clear written instructions on how to access and use the programme. Participants with poor digital literacy will receive an initial one-hour-long one-to-one training session with one of the study investigators. A basic briefing will be offered to participants who are deemed digitally literate. If participants wish to include a study partner to support their participation in the study, or if it is clear to the investigator that they will require such support, the study partner where needed will attend and participate in the training/orientation session.

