### Limitations

A limitation includes the single (investigator)-blinded design. Participants in the wait-list control group could hence alter their behaviour, potentially influencing study results and introducing bias. In addition, given the multiple assessments, there is a risk of the test burden on participants resulting in fatigue, inaccurate results including type 1 error inflation, or, indeed, withdrawal from the study [66]. This said, understanding this is a component of feasibility testing. To overcome this, the outcomes have been ordered in a hierarchy emphasising the feasibility measures over the secondary outcomes, and, if patients do experience fatigue, the assessments can be reduced to minimise this by adhering to the set order. Nevertheless, the potential for multiplicity and type I error inflation will be acknowledged and findings interpreted precisely and cautiously [67]. These exploratory analyses are intended principally to inform outcome selection, sample size estimation, and the design of a future definitive trial, and no formal hypothesis testing is intended. Another potential limitation is that, although some structured support is considered necessary in this feasibility study design, the scalability of this level of support in routine practice will require further evaluation. The multiple assessments also risk missing data. In this study, the missing outcome data will be assumed to be missing at random (MAR), and no formal imputation procedures will be undertaken. Instead, the extent and patterns of missing data will be described descriptively. This is appropriate, as many of the ways to impute missing data such as ‘last observation carried forward’ increase the risk of bias [68,69]. Finally, while the target sample size is modest and no formal sample size calculation was performed, there is no accepted guideline for feasibility studies; most select between 15–20 per arm with a widely used ‘rule of thumb’ of 12 [70]. This is in keeping with most feasibility studies, where the median sample size was found to be n = 30 [71].

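### Sections 2.1 and 2.2 contradict each other on blinding: investigators are to stay blinded, yet a study investigator trains some Sleepio participants one-to-one

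*Protocol article*

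**What the plan says.** Section 2.1 (Design) opens with the label: "REST is an investigator-blinded, randomised, controlled, two-arm, parallel feasibility study". It then divides the team. "The study coordinator will not be blinded to group allocation, as this is necessary to deliver training on the intervention" covers one side; on the other, "data collectors and controllers, statisticians, and site investigators will remain blinded to treatment assignment".

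Section 2.2 (Intervention and Comparator) describes the training. It is given after allocation and in one arm: "All individuals assigned to the intervention group will then receive a training/orientation session". The format depends on digital literacy, which is measured before randomisation. Those whose digital literacy is poor "will receive an initial one-hour-long one-to-one training session with one of the study investigators". For the other group, "A basic briefing will be offered to participants who are deemed digitally literate"; who gives this briefing is not stated.

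The Limitations section again calls the design single (investigator)-blinded and makes no exception for a training investigator. It also says that "the outcomes have been ordered in a hierarchy emphasising the feasibility measures over the secondary outcomes", and that assessments may be cut along this order if a patient tires.

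**The concern.** Participants know their arm, so blinding of the people who rate and judge is the only masking the trial has. It can protect only what those people score. Section 2.3.1 describes the CDR as rated by a clinician, and section 2.6.2 lists it as a follow-up outcome together with the MMSE and ADAS-Cog. Section 2.8 has adverse events graded and judged for their relation to the intervention, and their frequency belongs to the second objective.

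If an investigator who trained a participant later carries out any of these tasks, that judgement is made with the arm known. The one-to-one session exists only in the Sleepio arm, so the knowledge, and any bias that follows from it, is one-sided. Section 2.7 intends to use between-group effect sizes (Cohen's d) to plan a definitive trial, so a distorted estimate on a rated scale could carry over into that planning.

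**Working it through.** No arithmetic applies, and the protocol has no figure here to reproduce. The check is a comparison of the text.

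1. **Who is unblinded, and why.** Section 2.1 names the study coordinator and gives delivery of training as the reason. By the protocol's own reasoning, a trainer has to know the allocation.
2. **Who is blinded.** Section 2.1 sets site investigators, data collectors and controllers, and statisticians against the coordinator.
3. **Who trains.** Section 2.2 has one of the study investigators train intervention participants with poor digital literacy. Applying step 1, that investigator is unblinded for each participant trained.
4. **Can the two be squared?** Section 2.1 says site investigators and section 2.2 says study investigators, so a separate unblinded investigator is conceivable. None is named. Section 2.3 describes one memory clinic. Section 2.4 has the principal investigator or delegated clinicians from the memory clinic service do the screening. The label in section 2.1 and its repetition under Limitations allow no exception. As printed, the same task falls to a role declared unblinded and to a role declared blinded.
5. **Is the training investigator kept away from assessment?** Nothing in sections 2.1, 2.2, 2.6 or 2.8 says so. Nothing says the opposite either: data collectors are listed separately, and no rater is named for the CDR, MMSE or ADAS-Cog.
6. **Extent.** Thirty participants at 1:1 gives about 30 / 2 = 15 in the Sleepio arm. The one-to-one session is only for those with poor digital literacy, and their share is not stated. The number trained by an investigator therefore lies somewhere between none and about 15, and the document does not narrow it.
7. **Usability scales, as a separate risk.** The System Usability Scale (SUS) and UMUX-Lite are primary outcomes (section 2.6.1), and feasibility measures rank above the secondary ones (Limitations). Wait-list controls are offered the programme only after week 10 (section 2.1), so at that visit they have not used what the scales ask about. A blinded assessor who handled these scales could learn the arm from the answers. Whether an assessor will handle them is not stated.

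**The case against.** The strongest reply is that a trainer who knows the allocation does not by that fact unmask a rater. Section 2.1 lists data collectors apart from site investigators, does not say that the coordinator is the only unblinded person, and never assigns rating to the investigator who trains. This stands in part. It shows that loss of assessor blinding is a risk and not an established result. It does not remove the conflict over who trains, or the claim that investigators are blinded.

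The second reply concerns weight. Recruitment, retention, session completion and usability scores are not rater-scored. The secondary outcomes are exploratory and unpowered. Several of them, among them the ISI, DEMQOL and BC-CCI, are self-reported, so assessor blinding could not protect them anyway. This stands, and it limits the severity.

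A reader might infer three stronger points that the document does not support:

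- **The usability scales are bound to unmask the assessor before the CDR and ADAS-Cog.** Nothing limits SUS or UMUX-Lite to one arm, and nobody is named to administer them. Section 2.7 compares a bespoke usability questionnaire in both groups, which is hard to square with a wait-list design but does not show that the scales are given to one arm. The hierarchy under Limitations concerns emphasis and what to drop when patients tire. Only the CDR is described as clinician-rated; no rater is stated for the ADAS-Cog.
- **The statistician is unblinded by platform data.** The article does not say when those data reach the statistician, and that sequence is commonly left to the analysis plan.
- **A definite number of participants is unmasked.** Any such figure needs an assumed share with poor digital literacy, and would count those known to a trainer, not those known to a rater.

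**Conclusion.** The point holds as a contradiction between sections 2.1 and 2.2. Delivering training is the stated reason for unblinding the coordinator, and the same task is then given, for part of the Sleepio arm, to a member of the group described as blinded. A single such session is enough to make the unqualified investigator-blinded label untrue for that investigator.

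Whether rated outcomes or relatedness judgements are biased depends on whether the training investigator also makes them, which the article neither provides for nor rules out. The handling of SUS and UMUX-Lite is a secondary risk to the blinding of data collectors and not a stated contradiction.

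The severity is moderate. No feasibility conclusion turns on it, and the exposed outcomes are exploratory. Blinding lost during conduct cannot be restored, however, so the text should be settled before participants are trained.

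**What to change.** - **Training.** Amend section 2.2 so that all training, including the one-hour sessions, is given by the unblinded study coordinator. Alternatively, give it to a team member who does not rate outcomes (notably the CDR, MMSE and ADAS-Cog) and does not judge adverse-event relatedness, and add that person to the unblinded roles in section 2.1.
- **Label.** If neither is workable, drop the unqualified investigator-blinded description in section 2.1 and under Limitations, and state who is blinded and for which outcomes.
- **Usability scales.** State that SUS and UMUX-Lite are self-completed or collected by the coordinator, and not by the blinded assessor. Leave them where they stand in the order: moving them behind the cognitive ratings would expose primary outcome data to loss from fatigue.

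The cost is a change of wording and more work for the coordinator. At one hour each, the one-to-one sessions come to at most about 15 × 1 = 15 hours, reached only if every Sleepio participant has poor digital literacy, and spread over a six-month recruitment period. Collecting the usability scales adds a short task for each participant. No new role is needed if the coordinator takes this on.
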